## 1. Introduction

Optimum management of control of hypertension requires a multi-disciplinary approach including appropriate medication and compliance. Thiazide type diuretics,  $\beta$  blockers, Angiotensin Converting Enzyme inhibitors (ACEIs), Calcium channel blockers (CCBs) are established classes of antihypertensive drugs that are used as monotherapy or as fixed dose combinations (FDC).

However, there exists a population of patients who would require more than a single drug to achieve the target blood pressure control. A two-drug combination for most of the patients with stage 2 hypertension (moderate to severe hypertension) has been recommended by JNC 7 guidelines which include thiazide-type diuretic and ACEI or ARB or BB or CCB.

## 2. Study Rationale

Fixed dose combination (FDC) of Indapamide SR + Amlodipine is a new FDC for the Indian market and this proposed study is a part of the marketing approval review process in India. Indapamide SR and Amlodipine are available in the Indian market for past approximately 20 years and are individually marketed for the treatment of hypertension. They are also taken simultaneously to achieve target blood pressure control. For the first time, a pharmaceutically stable formulation is developed by the applicant for the purposes of compliance in the treatment; the efficacy and safety of this formulation in the clinical setting is planned to be evaluated through this phase III registration clinical trial.

## 3. Study Objectives

### 3.1 Primary Objective

The primary objective of the study is to assess the blood pressure reduction rates in moderate to severe hypertensive patients after treatment with an FDC (Indapamide S.R. 1.5 mg + Amlodipine 5 mg) given once daily in the morning during the study evaluation period.

### 3.2 Secondary Objectives

To access the safety and tolerability of Indapamide S.R. 1.5 mg + Amlodipine 5 mg

## **4. Study Design**

### 4.1 A multicentric, open, non-comparative study

### 4.2 Study flow-chart

[figure not shown]

### 4.3 Study Procedures

The trial will be carried at various select centres in India. It will be conducted in the Out-patient clinics by physicians.

The patients will need to undergo screening prior to their inclusion as stipulated in the protocol.

### 4.4. Study visits and assessments

#### 4.4.1 Pre selection visit

1) After the clinical diagnosis of hypertension in the subject the investigator will take the medical history of the patient and shall perform the physical examination. If the subject

is found eligible, an informed consent for participation will be obtained and a baseline ECG and laboratory investigations will be performed.

2) The investigator will ensure that the subject fulfills the eligibility criteria as per the inclusion and exclusion criteria stipulated in the protocol to participate in the study.

#### 4.4.2 Baseline Visit (Visit 1, Day 0)

At this visit following activities shall be performed:

Patient Demography, Medical History, Inclusion and Exclusion criteria, Clinical & vital examination and associated diseases, Current treatment for hypertension or any other concomitant medication, if applicable shall be documented on the case report form.

The blood pressure measurement at each visit shall be carried out as per the JNC VII guidelines as under:

For blood pressure measurement, the auscultatory method with a properly calibrated and validated instrument should be used. Patient should be seated quietly for at least 5 minutes in a chair (rather than on an examination table), with feet on the floor and arm supported at heart level. An appropriate-sized cuff (cuff bladder encircling at least 80 percent of the measuring arm) should be used to ensure accuracy. At least two measurements should be made.

The investigator shall provide the study medication to the patient for the next 15 days ( $\pm$  5 days) and will give necessary instructions regarding the administration. The investigator shall emphasize to every patient to take the medication every morning at the same time. He shall also instruct the patient not to take extra doses in case the dose has been missed. The investigator shall also inform the patient to contact him in case of any doubt or discomfort experienced. The patients will be asked to bring back the remaining study medication during the next visit.

During the study, at every follow-up (f/u) visit, heart rate and blood pressure will be measured and Adverse Events (AEs) if any shall be recorded. After enrollment, the trial drug shall be dispensed to each of the participant (daily dose of one tablet per day in

morning with breakfast) till his next study visit and subsequently thereafter till end of study.

#### 4.4.3 Follow up visit (Visit 2, Day 15 $\pm$ 5 days)

At the follow-up visit 2, the investigator shall conduct the clinical and vital examination of the patient. He shall check the compliance to the study medication and shall interview the patient for any undesirable effects experienced since the last visit. At each visit, the doctor will also confirm that each patient is complying with the prescription and not missing any doses. The unused study medicine shall be collected from the patient. The investigator shall dispense the medications for the next 15  $\pm$  5 days to the patients.

#### 4.4.4. Follow-up visit (Visit 3, Day 30 $\pm$ 5 days)

At the follow-up visit 3, the investigator shall conduct the clinical and vital examination of the patient. He shall check the compliance to the study medication and shall interview the patient for any undesirable effects experienced since the last visit. At each visit, the doctor will also confirm that each patient is complying with the prescription and not missing any doses. The unused study medicine shall be collected from the patient. The investigator shall dispense the medications for the next 15  $\pm$  5 days to the patients. Clinical and vital examination, Compliance to study drug, AEs if any shall be recorded.

#### 4.4.5 End of Study (Visit 4, Day 45 $\pm$ 5 days)

This is the end of study visit. The investigator shall conduct the clinical and vital examination of the patient. He shall check the compliance to the study medication and shall interview the patient for any undesirable effects experienced since the last visit. At each visit, the doctor will also confirm that each patient is complying with the prescription and not missing any doses. The unused study medicine shall be collected from the patient. Additionally laboratory investigations (section 4.4.6) and ECG shall be repeated at the end of study. The investigator shall prescribe the most appropriate medicine for the treatment of hypertension to the patient.

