#### 4.4.6 Laboratory Assessments

The laboratory investigations as under will be performed during screening and at end of study (Visit 4, Day 45± 5 days). All tests will be performed at laboratories associated with trial centers or otherwise defined before the initiation of the trial. 5 mL of blood and 30 mL of urine will be collected, each at visit 1 and visit 4 (total blood loss for each patient = not more than 10 mL)

The laboratory test will include -

|                |   |                                                                                                                 |
|----------------|---|-----------------------------------------------------------------------------------------------------------------|
| Hematology     | - | CBC, ESR                                                                                                        |
| Biochemistry   | - | Total Bilirubin, AST, ALT, Serum Creatinine, Blood urea, Fasting blood sugar, Serum Electrolytes, Lipid profile |
| Urine Analysis | - | Routine & microscopy                                                                                            |
| ECG            | - | Chest                                                                                                           |

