### 5. Study population

240 patients (30 patients per centre) will be included in the study satisfying the eligibility criteria as per the protocol, with an objective to obtain at least 200 patients completing the study.

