## **12. Ethical Requirements**

#### Informed Consent

Informed consent will be obtained from each subject. The investigator will give each subject full information about the nature, meaning and importance of the study & a description of the procedures to be followed by the subject, all in accordance with Declaration of Helsinki. They will further be given a description of any foreseeable risks and discomforts. Subjects will also be told that they have the right to opt out of the trial at anytime without having to give reasons and without prejudice to further treatment. Each subject will be given a copy of the subject information sheet and will be given sufficient time to consider the implications of the study before deciding whether or not to participate in the trial.

The Informed consent form must be signed by the subject and the investigator. At this time the subject must have the legal capacity and be able to comprehend the nature, meaning, importance and risks of the study and to make up his/her mind accordingly.

If the subject is illiterate, subject's legally acceptable representative (LAR) may understand and sign the Informed consent form.

If the subject and subjects LAR both are illiterate an impartial witness (a person, who is independent of the trial and who cannot be unfairly influenced by people involved in the trial) will attend the entire informed consent process and will read out the subject information sheet and the informed consent form in a language best known to the subject.

Signed Informed consent means the acceptance that the individual's data will be known to the Investigator, the sponsor and possibly the Regulatory Authorities.

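### On-treatment laboratory tests and ECG are required only at the Day 45 visit, so patients who leave earlier, or are on treatment when the study or a centre closes, have no protocol-required on-treatment laboratory or ECG value

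*Protocol*

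**What the plan says.** Laboratory tests and ECG are planned twice.

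- Before treatment: section 4.4.1 (pre-selection visit) says "a baseline ECG and laboratory investigations will be performed".
- On treatment: section 4.4.5 (Visit 4) says "Additionally laboratory investigations (section 4.4.6) and ECG shall be repeated at the end of study". Section 4.4.6 confirms the timing, "during screening and at end of study (Visit 4, Day 45± 5 days", and lists the ECG in the same table as haematology, biochemistry and urine analysis.

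Sections 4.4.3 and 4.4.4 (Visits 2 and 3) cover clinical and vital examination, compliance and undesirable effects, with no laboratory test or ECG. The laboratory row of the activity chart (section 23) is marked at pre-selection and Visit 4 only.

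The protocol foresees early stopping in several places. Section 5 says "240 patients (30 patients per centre) will be included in the study", "with an objective to obtain at least 200 patients completing the study". Section 12 gives patients the "right to opt out of the trial at anytime". Section 11 has the action taken on study drug recorded for adverse events. Section 19 provides for termination of the study and closure of single centres. None of these is linked to a closing assessment, and the activity chart has no column for one. Section 3.2 makes the "safety and tolerability of Indapamide S.R. 1.5 mg + Amlodipine 5 mg" the only secondary objective.

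**The concern.** The schedule makes on-treatment laboratory and ECG data depend on reaching Visit 4. Patients who leave before it may include those who tolerated the combination poorly, and for them nothing in the protocol requires creatinine, electrolytes, glucose, lipids, liver enzymes or an ECG while on treatment or just after it. If abnormal values are more frequent among early leavers, a summary of the available results would make the combination look safer than it is. The study has no control arm against which such a loss might show.

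The same applies if the study is terminated for a safety reason under section 19. Every patient then on treatment and short of Visit 4 would have no required on-treatment value.

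This is a matter of the visit schedule, which the protocol fixes. A statistical analysis plan cannot recover samples and tracings that were never taken.

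**Working it through.** **Inputs**

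- Patients to be included: 240 (section 5).
- Target number of completers: at least 200 (section 5).
- Required laboratory/ECG occasions after the start of treatment: Visit 4 only (sections 4.4.5 and 4.4.6, activity chart).
- Blood volume: 5 mL at each of two draws, limit 10 mL per patient (section 4.4.6).
- Dropout rate: not stated.
- Number of completers with an abnormal value, x: not stated; assumed below and shown over a range.

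**Step 1. The protocol's own figures.** 240 − 200 = 40, and 40/240 = 16.7%. In the other direction, 200/(1 − 40/240) = 240. The figures are consistent with a 16.7% allowance, but they also fit 200 × 1.20 = 240. Since no rate is given, the intended reasoning cannot be identified. The 40 is the largest loss compatible with the completer target.

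**Step 2. Required on-treatment laboratory/ECG assessments.** Before Day 45 ± 5: none. For a patient who leaves before Visit 4: none. If 40 leave, planned coverage is 200/240 = 83.3%.

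**Step 3. What the missing values could hide.** Suppose x of 200 completers are abnormal and none of the 40 others is measured. The rate among all 240 then lies between x/240 (none of the 40 abnormal) and (x + 40)/240 (all 40 abnormal).

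| x of 200 (assumed) | Rate in completers | Lowest rate in 240 | Highest rate in 240 |
|---|---|---|---|
| 0 | 0% | 0% | 40/240 = 16.7% |
| 4 | 2.0% | 4/240 = 1.7% | 44/240 = 18.3% |
| 10 | 5.0% | 10/240 = 4.2% | 50/240 = 20.8% |
| 20 | 10.0% | 20/240 = 8.3% | 60/240 = 25.0% |

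The width is always 40/240 = 16.7 percentage points.

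**Step 4. Direction.** With x = 10, the completer rate equals the overall rate when 2 of the 40 are abnormal: (10 + 2)/240 = 5.0%. With more than 2 of 40, the completer rate understates the overall rate; with fewer, it overstates it. The direction therefore depends on why patients leave, which the protocol cannot tell us.

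**Step 5. Blood limit.** One pre-treatment draw plus one closing draw in place of the Visit 4 draw is 5 + 5 = 10 mL, which is within the limit.

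**The case against.** Several points on the other side are sound and limit the claim.

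- A reader might infer that 40 patients are expected to drop out. Section 5 makes no such forecast. It sets a completer target, and 40 is what that target leaves room for; the actual loss could be smaller or larger.
- A reader might infer that early leavers will have no laboratory or ECG data at all. The protocol does not forbid unscheduled tests, and section 4.4.2 asks patients to contact the investigator about any discomfort. Only the absence of required data can be asserted.
- A reader might infer that a patient who stops the tablets is excluded from Visit 4. Nothing says so. Such a patient could attend and be tested, though perhaps well after the last dose. The protocol is silent on what happens.
- A reader might infer that the results are certain to be biased toward safety. The documents give no reasons for non-completion. Withdrawal of consent and closure of a slow-recruiting centre are possible alongside toxicity, and the lower bounds in the table lie at or below the completer rates.
- Section 16.2 describes the safety criterion through the side-effect profile, and adverse events are recorded at Visits 2, 3 and 4. Early leavers therefore contribute adverse events up to their last attended visit. The gap concerns laboratory and ECG findings only.
- The study flow-chart (section 4.2) and the overview figure (section 22) are not shown, so an early-withdrawal step in one of them cannot be ruled out.

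What remains is that the visit text and activity chart require no on-treatment laboratory test or ECG before Visit 4 and attach none to any form of early stopping. The protocol collects these measurements before and after treatment in a study whose only secondary objective is safety, so the side-effect wording does not make them irrelevant.

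**Conclusion.** The point holds in a limited form. Followed exactly, the protocol leaves patients who depart before Visit 4, or who are on treatment at study or centre closure, without a required on-treatment laboratory or ECG value. The completer target allows for up to 40 of 240 (16.7%), counting every non-completer as someone who leaves before Visit 4 and has no unscheduled test. On that basis any laboratory or ECG abnormality rate carries a worst-case uncertainty of 16.7 percentage points. Understatement of risk is plausible, because patients who stop for adverse events may be more likely to have abnormal values, but it is not shown. The range from 4.2% to 20.8% rests on an assumed 10 abnormal results among 200 completers and is a pair of bounds, not an estimate. The blood pressure criteria are not in question here. The change should be made because it is cheap and the data cannot be recovered later.

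**What to change.** Add to section 4.4.5, and as an extra column in the activity chart, wording such as: *For any patient who stops study medication or leaves the study early for any reason, and for any patient on treatment when the study or a centre is closed, the Visit 4 assessments (blood pressure, heart rate, adverse events, laboratory tests, ECG) are done at the time of stopping, as close to the last dose as possible. This sample replaces the Visit 4 sample.* Refer to it from sections 4.4.6, 12 and 19. If one of the figures not shown already contains such a step, the text and chart should be brought into line with it.

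The cost is one paragraph, one chart column and the effort of bringing early leavers back once. No patient has more than the two planned draws, so the 10 mL limit still holds. Planned coverage would rise from as low as 83.3% to at most 100%. Some patients will not return, so the gap is reduced and not closed.

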#### 4.4.6 Laboratory Assessments

The laboratory investigations as under will be performed during screening and at end of study (Visit 4, Day 45± 5 days). All tests will be performed at laboratories associated with trial centers or otherwise defined before the initiation of the trial. 5 mL of blood and 30 mL of urine will be collected, each at visit 1 and visit 4 (total blood loss for each patient = not more than 10 mL)

The laboratory test will include -

|                |   |                                                                                                                 |
|----------------|---|-----------------------------------------------------------------------------------------------------------------|
| Hematology     | - | CBC, ESR                                                                                                        |
| Biochemistry   | - | Total Bilirubin, AST, ALT, Serum Creatinine, Blood urea, Fasting blood sugar, Serum Electrolytes, Lipid profile |
| Urine Analysis | - | Routine & microscopy                                                                                            |
| ECG            | - | Chest                                                                                                           |

### 5. Study population

240 patients (30 patients per centre) will be included in the study satisfying the eligibility criteria as per the protocol, with an objective to obtain at least 200 patients completing the study.

### 6. Eligibility Criteria

#### 6.1 Inclusion Criteria

1. Newly diagnosed untreated hypertensive patients having a baseline blood pressure  $\geq 160/100$  mmHg) OR
2. Uncontrolled patients of hypertension with a baseline blood pressure  $\geq 140/90$  mmHg on monotherapy with a Calcium Channel Blocker (CCB)
3. Patients of either sex

4. With confirmed diagnosis of Stage II/ III (moderate to severe) hypertension, as per JNC 7 guidelines

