## 16. Biometry and statistical analysis

The data of the study will be statistically analysed using SPSS version 11 statistical programme using appropriate statistical tests.

16.1 Primary evaluation criteria: The primary evaluation criterion is the efficacy of the treatment in achieving the target blood pressure control. This will be evaluated as under:

- Reduction in blood pressure from baseline to end of study
- Blood pressure control rates observed in the patient population

16.2 Secondary evaluation criteria:

Safety and tolerance of this drug treatment in terms of side effects profile.

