## 23. Patient Activity Chart

| Activity                                               | Pre Selection Visit | Baseline visit, Visit 1 (D 0 ) | Follow-up visit, Visit 2 (D 15 ) | Follow-up visit, Visit 3 (D 30 ) | End of study visit, Visit 4 (D 45 ) |
|--------------------------------------------------------|---------------------|-------------------------------------------|---------------------------------------------|---------------------------------------------|------------------------------------------------|
| Informed Consent                                       | X                   | --                                        | --                                          | --                                          | --                                             |
| Blood pressure, Heart rate                             | X                   | X                                         | X                                           | X                                           | X                                              |
| Laboratory investigations                              | X                   | --                                        | --                                          | --                                          | X                                              |
| Eligibility Criteria                                   | X                   | X (based on lab reports)                  | --                                          | --                                          | --                                             |
| Demography, clinical characteristics & Medical history | X                   | --                                        | --                                          | --                                          | --                                             |
| Clinical examination                                   | --                  | X                                         | X                                           | X                                           | X                                              |
| Study medication to be provided                        | --                  | X                                         | X                                           | X                                           | --                                             |

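### As worded, one baseline blood pressure can both admit the patient and start the primary change, so with no control arm the reported reduction may include regression to the mean; the sections conflict on which reading does which job.

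*Protocol*

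**What the plan says.** Both entry routes in section 6.1 are tied to a baseline value. The untreated route takes "Newly diagnosed untreated hypertensive patients having a baseline blood pressure" of at least 160/100 mmHg. The second takes "Uncontrolled patients of hypertension with a baseline blood pressure" of at least 140/90 mmHg on CCB monotherapy.

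Section 16.1 lists two primary measures: "Reduction in blood pressure from baseline to end of study" and "Blood pressure control rates observed in the patient population". Section 4.1 describes "A multicentric, open, non-comparative study".

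Section 4.4.2 is the baseline visit, Visit 1 on Day 0. Among the items to be documented there are "Patient Demography, Medical History, Inclusion and Exclusion criteria".

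Two other places point elsewhere. Section 4.4.1 has the investigator check the eligibility criteria at the pre-selection visit. The activity chart in section 23 schedules blood pressure at both pre-selection and Visit 1, and its Visit 1 entry for eligibility reads "X (based on lab reports".

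No section says which reading is compared with the threshold, or which is the reference for the change.

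**The concern.** A reading selected for being high is, on average, above the patient's usual level. The next reading tends to be lower even if nothing has changed. If the selected reading is also the starting point for the change, that fall is reported as part of the reduction. A concurrent control would show the same fall and allow it to be subtracted, but this design has none.

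Section 2 presents the trial as a phase III registration study, and blood pressure reduction is its primary objective (section 3.1). An inflation of a few mmHg would go straight into the efficacy estimate. Which reading admits a patient is an entry rule, so it has to be fixed before enrolment and cannot be repaired at analysis.

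**Working it through.** **Plan's own figures.** The protocol gives 240 enrolled, 200 completers and 30 per centre, hence 240/30 = 8 centres and 40/240 = 16.7% loss. It gives no SD, expected reduction, alpha or power, so there is no stated figure on this point to reproduce. Every mean and SD below is an assumption.

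**One limit, closed form.** Let μ be the source mean, sb the between-patient SD, sw the visit-to-visit SD, c the cutoff, st = √(sb² + sw²) and z = (c − μ)/st. The expected fall with no true change is

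(sw²/st) × φ(z)/(1 − Φ(z)).

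- Systolic, c = 160, μ = 150, sb = 15, sw = 10: st = √325 = 18.03 and z = 0.555. The fall is (100/18.03) × (0.342/0.290) = 6.55 mmHg.
- Diastolic, c = 100, μ = 95, sb = 8, sw = 6: st = 10 and z = 0.5. The fall is 3.6 × (0.352/0.309) = 4.11 mmHg.

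The source mean matters. For the 160 cutoff with sb 12–15 and sw 8–10, the fall is 5.4–9.6 mmHg at μ = 145 but 2.3–3.9 mmHg at μ = 165.

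**Both pressures together, by simulation.** Assumptions: true blood pressure unchanged, means 145–155/92–97, sb 15/8, sw 10/6, correlation 0.6, 4 million draws per setting. The threshold pairs do not say whether both limits must be met or either suffices, so both versions are shown. Entries are mean falls, systolic/diastolic, in mmHg.

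| Entry rule | Reference = qualifying reading | Reference = separate reading not used for entry | Both visits must qualify, Day 0 = reference |
|---|---|---|---|
| 160/100, both limits | 6.3–8.6 / 3.9–5.2 | 0.0 / 0.0 | 4.2–5.6 / 2.6–3.5 |
| 160/100, either limit | 3.7–5.5 / 2.3–3.4 | 0.0 / 0.0 | 2.6–3.7 / 1.6–2.3 |
| 140/90, both limits | 2.6–4.2 / 1.7–2.7 | 0.0 / 0.0 | 1.8–2.9 / 1.2–1.9 |
| 140/90, either limit | 1.1–2.2 / 0.6–1.3 | 0.0 / 0.0 | 0.9–1.6 / 0.5–0.9 |

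A second set of assumptions (means 150/94 untreated and 142/90 on CCB, sb 12–15/8–10, sw 7–10/4.5–6.5) gives similar values with the qualifying reading as reference:

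- untreated, both limits: 3.7–8.4 / 2.3–5.3
- untreated, either limit: 2.2–4.9 / 1.5–3.3
- CCB route, either or both limits: 1.3–5.1 / 0.8–3.5

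**Would such an artefact be significant?** With 200 completers and an assumed SD of change of 12–15 mmHg, a paired comparison has 80% power for 2.80 × SD/√200 = 2.4–3.0 mmHg. Power is above 0.99 for a 5 mmHg artefact, but only about 0.33 (SD 12) to 0.23 (SD 15) for 1.3 mmHg.

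**Control rate.** The protocol gives no target in mmHg. Taking below 140/90 as an assumption, and true blood pressure unchanged, 1–2% of patients (160/100 entry) or 4–9% (140/90 entry) would count as controlled if both limits were needed for entry. If either sufficed, the figures are 2–5% and 7–15%.

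**The case against.** The strongest reply is that the protocol may already intend a clean design. Section 4.4.1 puts the eligibility check at pre-selection, and the chart rests the Visit 1 check on laboratory results. Nor is the word baseline reserved for Visit 1, since section 4.4.1 uses it for the pre-selection ECG. Recording the criteria at Visit 1 is also not the same as gating on that day's pressure. If only the pre-selection reading gates entry and Visit 1 is the reference, the selection effect is about zero. This stands, and a reader should not infer that the primary reduction is biased by construction. It does not settle the matter, because section 6.1 still names the baseline reading and no section assigns the threshold to pre-selection. The visits are also blurred: section 4.4.6 places the first laboratory sample both at screening and at Visit 1, and no interval between the two visits is stated.

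A reader might also infer that an inert tablet would be bound to succeed. The documents do not support that. Section 16 names no test against zero and no success rule. The control rate is a second primary measure with no baseline reference, and an inert tablet would look poor on it. At the low end of the assumed range the artefact would usually not reach significance.

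The CCB figures need care. Section 9 forbids other antihypertensives, so a truly inert tablet would also mean losing the previous CCB effect, which would work against the simulated fall. Those figures are the regression component alone, not a predicted change on an inert tablet.

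Finally, the analysis baseline could be defined in a statistical analysis plan. The entry rule could not.

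**Conclusion.** The point holds conditionally. Read literally, sections 6.1, 4.4.2 and 16.1 let one reading selected for being high both admit the patient and start the primary change, and section 4.1 provides no arm to remove the resulting fall. Sections 4.4.1 and 23 point the other way, so the text conflicts.

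If the literal reading is followed, the simulated inflation of the mean reduction is roughly 1 to 8 mmHg systolic and 1 to 5 mmHg diastolic. It is largest for the untreated route with both limits required. If both visits must qualify, it is smaller but does not vanish. The direction follows from the selection itself. The size rests on assumed means and variances, and the overall figure also depends on the mix of the two routes, which the protocol does not fix. The concern is with the change measure; the control rate is much less affected.

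**What to change.** - **Section 6.1:** state that the blood pressure thresholds of criteria 1 and 2 are assessed on the pre-selection reading. The threshold values stay as they are.
- **Sections 4.4.2 and 16.1:** define baseline for the change as the mean of the seated Visit 1 readings, taken before the first dose and on a different day from pre-selection. State that these readings are not used to accept or reject a patient on blood pressure. The Visit 1 eligibility check stays on laboratory results, as in the chart. Averaging within one visit does not replace the separate day, because it leaves visit-to-visit variation in place.
- **Reporting:** give the mean reduction as an estimate with a 95% confidence interval, and say that placebo and time effects cannot be separated from drug effect without a control.

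The cost is mainly wording, since the chart already schedules both readings. A centre that would have run the two visits on one day would need to separate them. Some patients will have Visit 1 values below the entry threshold, and the reported reduction will be somewhat smaller than under the literal reading. The change removes only the regression due to selection.
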